### Sample size

The number of samples required for this study was calculated based on weight as a main dependent variable. The results of a previous study were used to calculate the sample size [47]. Sample size was calculated with α = 0.05 and power of 80% (1-β = 0.8). the sample size in each group was determined to be 20 patients; assuming a drop of 20%, 25 patients will be admitted to each group.

$$\begin{array}{c}\mathrm S1=2.8\\\mathrm S2\;=2.9\\\mathrm{Sp}\;=\;8.125\\\mathrm\mu1-\mathrm\mu2=2.5\\\end{array}$$

$$\begin{array}{c}\mathrm n=\frac{2\mathrm{Sp}^2\left({\mathrm Z}_{1-{\displaystyle\frac{\mathrm a}2}}+{\mathrm Z}_{1-\mathrm\beta}\;\right)^2}{\left(\mathrm\mu1-\mathrm\mu2\right)^2}\end{array}$$

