### Study population

Patients with weight regain after bariatric surgery, and food addiction will be recruited from the Obesity Surgery Center of Sina Hospital and Rasoul Akram Hospital in Tehran.

Weight regain in this study was defined as: At least 18 months have passed since the surgery, and at least 10% of the lowest weight has returned. The diagnosis of food addiction will be based on the Food Addiction Questionnaire (Modified Yale Food Addiction Scale; mYFAS 2.0) [48]. Subjects who meet the inclusion criteria will be thoroughly informed about the protocol of the study. In addition, each participant will sign the informed consent form.

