### Randomization

This study is a triple-blind randomized controlled clinical trial. A simple method has been used for randomization. The randomization unit is Individual. Excel software has been used for randomization. Using unique codes as ID numbers, using random numbers generated by the software, participants were randomly assigned to the same volume in the intervention and placebo groups. (Description of randomization by Excel software: In the first step, we generated 50 random numbers according to the sample size, in the next step, we obtained the rank of these numbers obtained in the first step, and in the third step, we divided these numbers by 25, in the fourth step, the numbers that fell between zero and one were in the intervention group and the rest in the placebo group) The primary service method was used for allocation concealment, and someone outside our study performed allocation concealment and labeling of supplements.

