### Statistical analysis

In this study, data analysis will be performed by using SPSS version 21.0 (SPSS Inc, Chicago, Illinois) software. A paired t-test will be used to compare the mean of quantitative variables with normal distribution in each group between the beginning and the end of the study. The t-test will be used to compare the mean between the two groups at the beginning and end of the study. In the case of quantitative variables with non-normal distribution, Wilcoxon and Mann–Whitney tests are used, respectively. A repeated ANOVA test will be used for the variables measured three times during the study. Covariance analysis will be used to eliminate the effect of quantitative confounding factors. Quantitative confounding factors are physical activity and baseline values of the biochemical markers. A Chi-square test will be used to compare the qualitative variables between the two groups, and regression analysis will be used to eliminate the effect of qualitative confounding.

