## Discussion

Weight regain after bariatric surgery is one of the unpleasant events. The prevalence of weight regain depends on the type of surgery and how long it has been since surgery [5, 6]. Eating behaviors are one of the reasons for weight regain after bariatric surgery [7–11]. Food addiction is one of the eating behaviors that are directly related to the brain-intestine- axis. Recently, growing studies on the role of intestinal microbiota in the etiology and progression of eating disorders are underway [18]. There is a correlation between mood, hormonal changes, stress-induced inflammation, autonomic changes, eating behavior, and intestinal microbiota. It has been suggested that some bacterial species may cause dysregulated eating [20]. Intestinal microbiota affects eating behaviors by affecting the homeostatic and hedonic systems. However, in food addiction, a change in the Brain-Gut-Microbiome (BGM) system shifts this balance to hedonic mechanisms [17]. Hormones such as leptin, serotonin, and oxytocin, have an essential role in the hedonic and homeostatic system and result from eating behaviors and food addiction [21–25]. Bariatric surgery leads to anatomical, neurological, and physiological changes affecting the signaling of the homeostatic and hedonic systems, as well as changes in gastrointestinal hormones and intestinal microbiome, which profoundly affect eating behavior and weighing consequences [39].

It seems based on the available evidence, Probiotic supplementation by modifying the intestinal microbiome can lead to the improvement of food addiction and subsequent weight loss. Therefore, this study aimed to evaluate the effect of probiotic supplementation on the improvement of food addiction and its related hormones and the improvement of anthropometric indices in patients with food addiction and weight regain after bariatric surgery.

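### The stated quantitative adjustment factors leave out time since surgery, and nothing commits the analysis to surgery type, although the protocol ties weight regain to both

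*Protocol article*

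**What the plan says.** **Drivers of regain.** The Discussion states: "The prevalence of weight regain depends on the type of surgery and how long it has been since surgery". The Background makes the same statement about prevalence. In a separate list of influences on weight maintenance or regain, it puts type of surgery first.

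**Entry.** The Study population section defines regain as: "At least 18 months have passed since the surgery, and at least 10% of the lowest weight has returned". No upper limit on time is given. Neither that section nor the inclusion and exclusion criteria restrict the procedure.

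**Allocation.** The Randomization section says: "A simple method has been used for randomization". The mechanics are a single list: "we generated 50 random numbers according to the sample size". These numbers are ranked and split 25 and 25. No stratification factor is named.

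**Adjustment.** The Statistical analysis section plans covariance analysis for quantitative confounders and then says which they are: "Quantitative confounding factors are physical activity and baseline values of the biochemical markers". For qualitative variables it plans a chi-square comparison of the groups and a regression to remove confounding, without naming a factor.

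**The concern.** The protocol singles out two patient characteristics as bearing on regain, admits patients across their whole range, and then writes a list of quantitative adjustment factors that omits the one that is quantitative. Surgery type could enter through the qualitative regression, but nothing commits the trial to it. The same list names baseline biochemical values but not baseline weight, although weight is the variable on which the trial is sized.

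With 20 to 25 patients per arm, the arms can easily differ on such a factor. If it also predicts weight change over 12 weeks, the unadjusted contrast in that trial moves for reasons unrelated to the capsule, and the residual variance is larger than it need be. Choosing the covariates after seeing an imbalance would be open to challenge as post hoc.

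**Working it through.** **1. The plan's own figure.** Inputs from the Sample size section: SDs 2.8 and 2.9, difference 2.5 in weight (no unit printed), two-sided α 0.05, power 80%. The pooled variance is (2.8² + 2.9²)/2 = 8.125. The article prints this value as Sp, but it is a variance; the pooled SD is 2.85. That labelling slip does not affect this point.

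n = 2 × 8.125 × (1.960 + 0.842)² / 2.5² = 20.4 per group, against the stated 20. Dropout: 20/(1 − 0.20) = 25. The text reads: "the sample size in each group was determined to be 20 patients; assuming a drop of 20%, 25 patients will be admitted to each group". The figures reproduce to within rounding.

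**2. Chance of an imbalance.** Let K of N patients have a given operation, and let n go to each arm. The number X in one arm is hypergeometric, P(X = x) = C(K, x) C(N − K, n − x) / C(N, n), and the arm difference is |2x − K|/n. The documents give no prevalence, so K is assumed.

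| N, n per arm | K (share) | Gap ≥ 20 points when | Probability |
|---|---|---|---|
| 50, 25 | 25 (50%) | x ≤ 10 or ≥ 15 | 0.258 |
| 50, 25 | 15 (30%) | x ≤ 5 or ≥ 10 | 0.217 |
| 40, 20 | 20 (50%) | x ≤ 8 or ≥ 12 | 0.343 |
| 40, 20 | 12 (30%) | x ≤ 4 or ≥ 8 | 0.301 |

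At a share of 20% the probabilities are 0.074 and 0.235. A gap of at least 30 points in a 50% factor has probability 0.023 at 25 per arm and 0.113 at 20.

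For time since surgery, the standardised arm difference has SE √(2/n): 0.283 at 25 per arm and 0.316 at 20. A gap of at least 0.5 SD has probability about 8% and 11% (normal approximation).

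**3. What an imbalance does to the estimate.** Let D be the assumed difference in 12-week weight change between the two levels of the factor. The shift in the treatment contrast is D × gap. For D from 1 to 3 and gaps of 20 to 30 points it runs from 1 × 0.2 = 0.2 to 3 × 0.3 = 0.9, which is 8% to 36% of the 2.5 target.

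**4. Error rate and power.** 20,000 simulated trials per setting: 20 per arm, a 50% two-level factor, total variance held at 8.125 (residual variance 8.125 − D²/4), unadjusted t-test against covariance analysis on the factor.

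| Assumed D | Type I error, all trials, unadjusted | Type I error when gap ≥ 20 points, unadjusted | Power unadjusted | Power adjusted |
|---|---|---|---|---|
| 1 | 0.051 | 0.057 | 0.77 | 0.77 |
| 2 | 0.053 | 0.071 | 0.77 | 0.81 |
| 3 | 0.050 | 0.096 | 0.77 | 0.88 |

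**5. The price if the factors do not matter.** Same setting, true difference 2.5, with covariates unrelated to outcome. Power falls from 0.77 to about 0.75 with two added terms (time, and surgery in two groups) and to 0.73-0.74 with three (surgery in three groups). Type I error stays at 0.05.

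**The case against.** A reader might infer that the analysis ignores both factors. The text does not support that. The closed list covers quantitative factors only, and the section goes on to plan a regression for qualitative confounders. Surgery type may be among them, and an article can fairly leave that list to a fuller document. This objection stands for surgery type. It does not help time since surgery, because the article states which quantitative factors it means and this one is not there.

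A reader might also infer that the omission biases the trial or lets natural course pass for a probiotic effect. It does not, in that sense. Chance imbalance is already reflected in the standard error, nothing favours one arm, and overall type I error is 0.050-0.053 in the simulation. Only the error rate conditional on an imbalance rises.

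A third tempting reading is that the protocol says these factors drive the trial's outcome. The statements concern the prevalence of regain, and the Background's separate list of influences names surgery type but not time since surgery. Everyone enrolled has already regained weight, and the outcome is change over 12 weeks on a hypocaloric diet with CBT. No statement links either factor to that change, so every value of D is an assumption. At D = 1, adjustment gains nothing.

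Two smaller points also stand. Stratification is not obligatory at this size. And covariates entered as main effects would not address any difference in how the probiotic works after different operations.

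**Conclusion.** The point holds as a modest gap in a stated covariate list. The protocol attaches importance to two characteristics, omits one from its named quantitative factors and does not commit to the other. What is at stake is precision, and protection against an unlucky allocation in a single small trial. It is not systematic bias.

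A gap of at least 20 points in a two-level factor has probability 22-26% at 25 per arm and 30-34% at 20 per arm, assuming a share of 30-50%. If D were 2 to 3, adjustment would raise power from 0.77 to 0.81-0.88, and the unadjusted type I error in imbalanced trials would be 0.07 to 0.10. If D were 1, there would be almost no difference.

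The figures at 20 per arm and the 5% overall error assume that losses are unrelated to these factors. The plan analyses only patients who take more than 90% of their supplements, so that is an assumption and not something randomisation guarantees.

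**What to change.** Before unblinding, amend the Statistical analysis section so that the between-group covariance model for weight and the other outcomes includes, as pre-specified baseline covariates:

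- time since surgery, continuous, in months;
- type of surgery, grouped into a few categories fixed in advance;
- the baseline value of the outcome being analysed, including baseline weight.

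Tabulate time since surgery and surgery type by arm. Keep the existing randomisation list, since enrolment has begun.

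The cost is mainly wording. The surgery date is already needed to check the 18-month criterion, and the recruiting obesity surgery centres should hold the operation type. Time and surgery type use two to three degrees of freedom. If neither predicts outcome, power falls by about 2 to 4 points at 20 per arm, which is why the surgery categories should be few.

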### Ethical considerations

Patients with weight regain after bariatric surgery, and food addiction who meet the inclusion criteria will be thoroughly informed about the study's protocol. The protocol of this study was approved by the ethics committee of Shahid Beheshti University of Medical Sciences and conformed with the declaration of Helsinki (approved number IR.SBMU.NNFTRI.REC.1400.099).

### Modification of study

Any modifications to the protocol, such as changes in the study objectives, study design, study method, study intervention, or sample size that affect the interests or safety of the patient, will be agreed upon by NNFTRI (National Nutrition and Food Technology Institute) and approved by the ethics committee of Shahid Beheshti University of Medical Sciences before implementation. NNFTRI will agree upon minor corrections that do not affect the way of the study.

## Discussion

Weight regain after bariatric surgery is one of the unpleasant events. The prevalence of weight regain depends on the type of surgery and how long it has been since surgery [5, 6]. Eating behaviors are one of the reasons for weight regain after bariatric surgery [7–11]. Food addiction is one of the eating behaviors that are directly related to the brain-intestine- axis. Recently, growing studies on the role of intestinal microbiota in the etiology and progression of eating disorders are underway [18]. There is a correlation between mood, hormonal changes, stress-induced inflammation, autonomic changes, eating behavior, and intestinal microbiota. It has been suggested that some bacterial species may cause dysregulated eating [20]. Intestinal microbiota affects eating behaviors by affecting the homeostatic and hedonic systems. However, in food addiction, a change in the Brain-Gut-Microbiome (BGM) system shifts this balance to hedonic mechanisms [17]. Hormones such as leptin, serotonin, and oxytocin, have an essential role in the hedonic and homeostatic system and result from eating behaviors and food addiction [21–25]. Bariatric surgery leads to anatomical, neurological, and physiological changes affecting the signaling of the homeostatic and hedonic systems, as well as changes in gastrointestinal hormones and intestinal microbiome, which profoundly affect eating behavior and weighing consequences [39].

It seems based on the available evidence, Probiotic supplementation by modifying the intestinal microbiome can lead to the improvement of food addiction and subsequent weight loss. Therefore, this study aimed to evaluate the effect of probiotic supplementation on the improvement of food addiction and its related hormones and the improvement of anthropometric indices in patients with food addiction and weight regain after bariatric surgery.

### Trial status

This trail is in the enrolment stage.

### Protocol version

Recruitment began on June 2022 and is expected to be completed on June 2023.

## Data Availability

Not applicable.

## Abbreviations

mYFAS: Modified yale food addiction scale
MET: Metabolic equivalent of task
TFEQ-R18: Three-Factor Eating Questionnaire
